**Outcome measures**

Primary outcome

Comprehensive complication index 30 days postoperatively

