#### Sample size

Sample size is calculated based on primary outcome, Comprehensive complication index (CCI). CCI is based on Clavien-Dindo (C-D) classification, and CCI takes into account cumulative burden of complications better than C-D classification (Slankamenac et al., 2014). Thus CCI is more sensitive and requires smaller sample size compared to C-D classification. Clinically relevant difference in CCI is set at 10 points. This study will aim to show that cortisone-group does not have more than 9 CCI points more than in the pasireotide-group. Standard deviation (SD) is estimated to be 20 based on earlier publications. Based on sample size calculations 62 patients are required per group to show this, thus total 124 patients.

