## **References**

Laaninen M, Sand J, Vasama K, Laukkarinen J. Whipplen leikkauksen jälkeisiä komplikaatioita voidaan vähentää hydrokortisonihoidolla. *Randomoitu*

plasebokontrolloitu tutkimus. Suomen Kirurgiyhdistys ry 2015 36;4

Collected parameters

Name

Social security number

Date of birth

Gender (1 = male, 2 = female)

Charlson comorbidity index

Medication

Anticoagulation (0 = no, 1 = yes)

Immunosuppression (0 = no, 1 = yes)

Cortisone (0 = no, 1 = yes)

Date of diagnosis of pancreatic tumor (suspicion) (=computed tomography date)

Preoperative diagnosis (1 = pancreatic cancer, 2 = cholangiocarcinoma, 3 = IPMN, 4 = NET, etc)

Neoadjuvant therapy (0 = no, 1 = gemcitabine, 2 = folfirinox, 4 = chemoradiotherapy, 4 = other)

Randomization group (1 = signifor, 2 = cortisone)

Date of surgery

Type of surgery (1 = whipple, 2 = distal resection, 3 = enucleation, 4 = median pancreatectomy, 4 = exploration, 5 = total pancreatectomy, 6 = other)

Venous resection (0 = no, 1 = portal/SMV, tangential or end-to-end, 2 = porta/SMV,

Arterial resection (0 = no, 1 = yes)

Pancreaticojejunostomytype (1 = Heidelberg, 2 = [name], 3 = other)

Consistency of pancreas (1 = hard, 2 = soft, normal)

Pancreatic duct at operation (1 = small, normal, 2 = dilated)

Pancreatic duct size, computed tomography, mm

Drains (0 = no, 1 = one drain, 2 = two drains)

Was study drug continued after operation (1 = yes, 2 = no, hard pancreas/dilated duct in patient undergoing whipple, 3 = no, no operation, 4 = no, total pancreatectomy)

Complications, 30 days from operation

Pancreatic fistula, ISGPS grade

DGE, ISGPS grade

Postop haemorrhagia, ISGPS grade

First complication, C-D class

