First complication, description (1 = pancreatic fistula, 2 = DGE, 3 = postop haemorrhagia, 4 = pulmonary embolism, 5 = pneumonia, 6 = UTI, 7 = superficial wound infection, 8 = deep wound infection, etcetc)

Second complication, C-D class

Second complication, description (1 = pancreatic fistula, 2 = DGE, 3 = postop haemorrhagia, 4 = pulmonary embolism, 5 = pneumonia, 6 = UTI, 7 = superficial wound infection, 8 = deep wound infection, etcetc)

Third complication, C-D class

Third complication, description (1 = pancreatic fistula, 2 = DGE, 3 = postop haemorrhagia, 4 = pulmonary embolism, 5 = pneumonia, 6 = UTI, 7 = superficial wound infection, 8 = deep wound infection, etcetc)

Fourth complication, C-D class

Fourth complication, description (1 = pancreatic fistula, 2 = DGE, 3 = postop haemorrhagia, 4 = pulmonary embolism, 5 = pneumonia, 6 = UTI, 7 = superficial wound infection, 8 = deep wound infection, etcetc)

Fifth complication, C-D class

Fifth complication, description (1 = pancreatic fistula, 2 = DGE, 3 = postop haemorrhagia, 4 = pulmonary embolism, 5 = pneumonia, 6 = UTI, 7 = superficial wound infection, 8 = deep wound infection, etcetc)

Sixth complication, C-D class

Sixth complication, description (1 = pancreatic fistula, 2 = DGE, 3 = postop haemorrhagia, 4 = pulmonary embolism, 5 = pneumonia, 6 = UTI, 7 = superficial wound infection, 8 = deep wound infection, etcetc)

Postoperative amylase level at day 3

Postoperative drain amylase level at day 3

Postoperative blood sugar level, highest during hospital stay

Date of commencement of normal per oral feeding

Date of discharge

Destination of discharge (1 = home, 2 = primary care ward, 3 = referring hospital)

Referring hospital's name (1 = Helsinki University Hospital, 2 = Lappeenranta, 3 = Lahti, 4 = Kotka, etc)

PAD

Histology (1 = pancreatic ductal adenocarcinoma, 2 = cholangiocarcinoma, 3 = IPMN, 4 = NET, etc)

pT category

pN category

pM category  
Number of examined lymph nodes  
Number of metastatic lymph nodes  
R category

Re-admission, 30 days (0 = ei, 1 = yes)

Reason, free text

Was the blinding unmasked to treating doctors (0 = ei, 1 = yes, inadvertently, 2 = yes, advertently unmasked)

Reason, free text

Date of study drug stopping

Adverse event of study drug (0 = no adverse events, 1 = nausea, 2 = elevated blood sugar, etc)

Postoperative outpatient clinic visit (0 = no, 1 = yes, Helsinki University Hospital)

Adjuvant therapy (0 = no, 1 = gemcitabine, 2 = folfirinox, etcetc)

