Date of commencement of adjuvant therapy

Recurrence (0 = no, 1 = local, 2 = liver, 3 = lungs, 4 = peritoneal carcinosis, 5 = multiple)

Date of recurrence

Death (0 = no, 1 = yes, caused by pancreatic tumor, 2 = yes, unrelated to pancreatic tumor, 3 = yes, surgery complication)

Date of death

Last date of follow-up

Remission (0 = no, 1 = yes)

Patient withdrawn consent (0 = no, 1 = yes)

Date of withdrawal

(the study protocol in Finnish)

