### **Kerättävät parametrit**

Nimi  
Sotu

Syntymäaika

Sukupuoli (1=mies, 2=nainen)

Charlson comorbidity index

Lääkitykset

Antikoagulaatio (0 = ei, 1 = kyllä)

Immunosuppressio (0 = ei, 1 = kyllä)

Kortisoni (0 = ei, 1 = kyllä)

Haimatumori(epäilyn) diagnoosipvm (=TT-kuvaus)

Preop diagnoosi (1 = haimasyöpä, 2 = kolangioma, 3 = IPMN, 4 = NET, jne)

Neoadjuvanttihoito (0 = ei, 1=gemsitabiini, 2=folfirinox, 3=kemosäde, 4=muu)

Randomisaatioryhmä (1 = signifor, 2 = kortisoni)

Leikkauspvm

Leikkaustyyppi (1 = whipple, 2 = distaalinen resektio, 3 = enukleatio, 4 = mediaani pankreatektomia, 5 = eksploraatio, 6 = totaalipankreatektomia, 7 = muu)

Venaresektio (0 = ei, 1 = porta/VSM, tangentiaali tai pää-päättävasten, 2 = porta/VSM,

Arteriaresektio (0 = ei, 1 = kyllä)

Pankreatikojunostomiatyyppi (1 = Heidelberg, 2 = [name], 3 = muu)

Haiman konsistenssi (1 = kova, 2 = pehmeä, normaali)

Haimatiehyen koko leikkauksessa (1 = pieni, normaali, 2 = laajentunut)

Haimatiehyen koko, TT kuva, mm

Dreenit (0 = ei, 1 = yksi dreeni, 2 = kaksi dreeniä)

Jatkettiin tutkimuslääkettä (1=kyllä, 2=ei, kova haima/iso tiehyt whipple potilaalla, 3=ei, ei leikkausta, 4=ei, totaalipankreatektomia)

Komplikaatiot, 30vrk leikkauksesta

Haimafisteli, ISGPS grade

DGE, ISGPS grade

Postop hemorrhagia, ISGPS grade

1. komplikaatio, C-D luokka

1. komplikaatio, kuvaus (1 = haimafisteli, 2 = DGE, 3 = postop vuoto, 4 = keuhkoembolia, 5 = pneumonia, 6 = VTI, 7 = pinnallinen haavainfektio, 8 = syvä haavainfektio, jne)

2. komplikaatio, C-D luokka

2. komplikaatio, kuvaus (1 = haimafisteli, 2 = DGE, 3 = postop vuoto, 4 = keuhkoembolia, 5 = pneumonia, 6 = VTI, 7 = pinnallinen haavainfektio, 8 = syvä haavainfektio, jne)

3. komplikaatio, C-D luokka

3. komplikaatio, kuvaus (1 = haimafisteli, 2 = DGE, 3 = postop vuoto, 4 = keuhkoembolia, 5 = pneumonia, 6 = VTI, 7 = pinnallinen haavainfektio, 8 = syvä haavainfektio, jne)

4. komplikaatio, C-D luokka

4. komplikaatio, kuvaus (1 = haimafisteli, 2 = DGE, 3 = postop vuoto, 4 = keuhkoembolia, 5 = pneumonia, 6 = VTI, 7 = pinnallinen haavainfektio, 8 = syvä haavainfektio, jne)

5. komplikaatio, C-D luokka

5. komplikaatio, kuvaus (1 = haimafisteli, 2 = DGE, 3 = postop vuoto, 4 = keuhkoembolia, 5 = pneumonia, 6 = VTI, 7 = pinnallinen haavainfektio, 8 = syvä haavainfektio, jne)

6. komplikaatio, C-D luokka

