6. komplikaatio, kuvaus (1 = haimafisteli, 2 = DGE, 3 = postop vuoto, 4 = keuhkoembolia, 5 = pneumonia, 6 = VTI, 7 = pinnallinen haavainfektio, 8 = syvä haavainfektio, jne)

Postoper amylaasio 3vrk:na, pitoisuus

Postoper dreeni-amylaasi 3vrk, pitoisuus

Postoper verensokeri, suurin pitoisuus hoitojaksolla

Milloin aloittanut tavallisen ruuan, pvm

Kotiutumispäivä, pvm

Kotiutuminen (1=kotiin, 2=TK vuodeos, 3=oman alueen sairaala)

Oman alueen sairaala (1 = HYKS, 2=Lappeenranta, 3=Lahti, 4=Kotka, jne)

PAD

Histologia (1=haiman dukt adenoca, 2=kolangioca, 3=IPMN, 4=NET,jne)

pT-luokka

pN-luokka

pM-luokka

Tutkittujen imusolmukkeiden määrä

Metastaattisten imusolmukkeiden määrä

R-luokka

Re-admissio, 30vrk (0 = ei, 1=kyllä)

Syy, vapaa kenttä

Paljastuiko randomisaatio hoitaville lääkäreille (0 = ei, 1 = kyllä, vahingossa, 2 = kyllä, sokkoutus purettiin tarkoituksellisesti)

Syy, vapaa kenttä

Randomisaatiolääkkeen lopetuspäivä, pvm

Randomisaatiolääkkeen mahdolliset haitat (0 = ei haittoja, 1 = pahoinvointi, 2 = kohonneet verensokerit, jne)

Jälkitarkastus kir pkl (0 = ei, 1=kyllä, HYKS)

Adjuvanttihoito (0 = ei, 1=gemsitabiini, 2=folfirinox, jne)

Adjuvanttihoidon aloituspäivä, pvm

Residivointi (0 = ei, 1=paikallinen, 2=maksa, 3=keuhkot, 4=peritoneaalikarsinoosi, 5=multippeli)

Residivoinnin toteamispäivä, pvm

Kuollut (0 = ei, 1=kyllä, haimatuumorin aiheuttama, 2=kyllä, ei haimatuumoriin liittyvä, 3=kyllä,leikkauskomplikaatio)

Kuolinpäivä, pvm

Viimeinen seurantapäivä, pvm

Remissiossa (0 = ei, 1=kyllä)

Potilas halunnut keskeyttää tutkimuksen (0 = ei, 1=kyllä)

Keskeyttämispäivä, pvm

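### The parameter list holds the Clavien-Dindo class of only six complications, so the CCI would be understated, without any visible gap, in a patient who has more than six within 30 days

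*Protocol*

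**What the plan says.** The Outcome measures section names one primary outcome: "Comprehensive complication index 30 days postoperatively". The Sample size section gives the reason for choosing it: "CCI takes into account cumulative burden of complications better than C-D classification".

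The data behind it are set out in Appendix 1, the list of collected parameters that follows the References. Under the heading for complications within 30 days, the list runs from "First complication, C-D class" to "Sixth complication, C-D class". Each slot has a grade and a coded description, and the code list names eight types and is left open-ended. After the sixth slot the list moves on to amylase levels. The Finnish list (Kerättävät parametrit) has the same limit, ending with "6. komplikaatio, C-D luokka" and "6. komplikaatio, kuvaus".

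Neither version has a seventh slot, a field for further complications, a field for the CCI itself, or a rule on whether slots are filled by time or by severity.

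Some related items are collected elsewhere in the list. Examples are "Pancreatic fistula, ISGPS grade" (with matching items for delayed gastric emptying and haemorrhage), a free-text reason for readmission, and "Death (0 = no, 1 = yes, caused by pancreatic tumor", which continues with other causes and a date.

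**The concern.** A cumulative index is only as complete as the events entered into it. The protocol picks the CCI because it counts all complications together, then limits the number that can be graded. A seventh non-fatal event has nowhere to have its Clavien-Dindo class recorded. The description codes alone name more types than there are slots.

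The loss would also be silent. The protocol's Statistical analysis plan section promises to report missing data, but a patient with six filled slots looks complete. An analysis plan written later cannot recover grades that were never collected.

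For an affected patient the error has one sign: leaving out an event can only lower the CCI. If the omitted event were the worst one, the secondary outcome based on Clavien-Dindo class would be understated as well. At stake is a bias in the mean difference on which non-inferiority is judged, if the two arms lose different amounts.

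**Working it through.** **Inputs from the protocol.** Margin 9 CCI points, SD 20 and 62 patients per group (Sample size). One-sided 5% level through a 90% confidence interval (Statistical analysis plan). Allocation 1:1 (Randomization). Power is not stated, so 80% is assumed.

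**Step 1: reproduce the plan's figure.** n per group = 2 × SD² × (z0.95 + z0.80)² / margin² = 2 × 400 × (1.645 + 0.842)² / 81, which is just over 61 and rounds up to 62. This matches the protocol.

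**Step 2: standard error of the mean difference.** SE = 20 × √(2/62) = 3.59. Power with no true difference is Φ(9/3.59 − 1.645) = 0.805.

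**Step 3: bias from the limit.** The mean of an arm falls by (share of its patients with more than six complications) × (CCI points each loses). The bias in the difference is that fall in one arm minus the fall in the other. The documents give neither the share nor the loss, so both are assumed ranges. For scale, one patient in 62 is 1.6%, and 5% is about three patients.

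Suppose the true difference is exactly 9 points against cortisone. The one-sided type I error is then Φ(bias/3.59 − 1.645). In the table, the share and loss are those of the cortisone arm.

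| Share | Points lost each | Bias, all loss in cortisone arm | Type I error | Bias if pasireotide arm loses half as much | Type I error |
|---|---|---|---|---|---|
| 1% | 5 | 0.05 | 0.0515 | 0.025 | 0.0507 |
| 1% | 10 | 0.10 | 0.0529 | 0.05 | 0.0515 |
| 5% | 5 | 0.25 | 0.0576 | 0.125 | 0.0537 |
| 5% | 10 | 0.50 | 0.0661 | 0.25 | 0.0576 |
| 10% | 20 | 2.00 | 0.1383 | 1.00 | 0.0859 |

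The last row is an extreme case, shown only as an outer bound. If both arms lose the same amount, the bias is zero and the error stays at 0.05.

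**Step 4: the opposite direction.** If the loss falls in the pasireotide arm, cortisone looks relatively worse. With a bias of 0.5 and no true difference, power is Φ((9 − 0.5)/3.59 − 1.645), about 0.765 instead of 0.805.

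**Step 5: is a loss of 5 to 10 points plausible?** The protocol does not give the CCI formula. As an illustration only, assume that the CCI is half the square root of summed weights: grade I 300, II 1750, IIIa 2750, IIIb 4550, IVa 7200. Six grade II events score √10500 / 2 = 51.2. An omitted seventh event would then cost 0.7 (grade I), 4.1 (II), 6.3 (IIIa), 10.1 (IIIb) or 15.3 (IVa) points. The range of 5 to 10 lies in the middle of this spread. Steps 1 to 4 do not depend on these weights.

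**The case against.** The strongest reply is that the limit may never operate. It matters only for a patient with seven or more separate complications in 30 days, and the protocol gives no expected number per patient. Appendix 1 is a list of parameters, loosely drafted, and the case form itself is not shown. The Outcome measures section defines the CCI without any limit of six. Part of a severe course is also recorded elsewhere: an omitted haemorrhage would still have an ISGPS grade, and a death would still be recorded.

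Much of this stands, and it sets the size of the point. It does not remove it. An ISGPS grade, a readmission reason or a death entry does not give the Clavien-Dindo class of a non-fatal seventh event. The ISGPS items could reveal a gap for only three types of complication. As written, the list is the only place in the protocol where the grades for the primary outcome are collected.

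A reader might infer more than the documents support:

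- **That the most severely ill patients are the ones cut off.** The limit acts on the number of events, not on severity. A patient with a few grave complications is fully recorded.
- **That the slots run in order of occurrence, so late severe events drop out.** No order is stated and the slots carry no dates. If they were filled by severity, only the mildest events would be lost.
- **That the loss exceeds the non-inferiority margin.** One patient may lose more than 9 points under the assumed weights, but the margin applies to a difference in means.
- **That the error always helps cortisone pass.** It does so only if the cortisone arm loses more, and Step 4 shows the reverse case.

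**Conclusion.** The gap is real but minor. Both language versions collect a Clavien-Dindo class for at most six complications, with no overflow field and no rule on order or selection. The CCI would therefore be understated in any patient with more than six complications within 30 days, and nothing in the data would flag it.

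Whether any patient will be affected cannot be told from the documents. If 1% to 5% of one arm lose 5 to 10 points each, the mean difference moves by 0.05 to 0.5 points. With all of that loss in the cortisone arm, the one-sided type I error rises from 0.05 to at most about 0.066. These results rest on assumed shares and losses, on the protocol's SD of 20 and on its full sample size. The case for acting is that the error is avoidable and lies in the primary outcome, not that it is likely to change the trial's conclusion.

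**What to change.** In both language versions of Appendix 1, replace the six numbered slots with a repeating complication row (description and Clavien-Dindo class) without an upper limit. Add one sentence stating that every complication within 30 days enters the CCI. With all events recorded, the order of entry no longer matters.

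If recruitment has begun, go back to the source records of any patient with all six slots filled and add further events before the CCI is computed. This should be done without regard to treatment group.

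The cost is a small edit to the list and a re-check of whichever patients have six entries. It needs no extra visits or patients, and 62 per group is unchanged.

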### **Tausta**

Haimaleikkauksiin liittyy merkittävä riski komplikaatioihin, erityisesti haimasuolisauman pettämiseen, joka johtaa haimafisteliin ja sitä kautta myös muihin komplikaatioihin. Lukuisia eri menetelmiä on tutkittu tämän komplikaation vähentämiseksi. Hiljattain julkaistiin Yhdysvalloista suuri randomoitu sarja, jossa osoitettiin pasireotidin vaikuttavuus haimafistelien vähentämiseksi (Allen ym., 2014). Tämän tutkimuksen perusteella klinikassamme aloitettiin pasireotidin käyttö haimafistelien vähentämiseksi ns. korkean riskin potilailla, joilla haima on pehmeä ja/tai haimatiehyt on kapea. Viime vuonna kuitenkin suomalainen tutkimusryhmä julkaisi vastaavanlaisen tutkimuksen, jossa osoitettiin perioperatiivisen kortisolihoidon vähentävän komplikaatioita ja fisteleitä kutakuinkin saman verran kuin pasireotidi toisessa julkaisussa (Laaninen ym. 2014, 2015). Molemmissa tutkimuslääkettä verrattiin placeboon, eikä näitä kahta lääkettä vertailevaa tutkimusta ole tehty. Koska pasireotidi on kalliimpi hoito kuin kortisoni, on tärkeää selvittää ovatko lääkkeiden estovaikutus samaa luokkaa, jolloin voitaisiin siirtyä käyttämään kortisonia pasireotidin sijaan.

### **Hypoteesi**

Kortisoni ei ole huonompi kuin pasireotidi haimafistelien ja komplikaatioiden ilmaantumisen vähentämisessä

### **Menetelmät**

#### **Tutkimuspaikat**

Vatsakeskus, Helsingin yliopistollinen keskussairaala

#### **Interventoryhmät**

##### **1) Perioperatiivinen pasireotidihoito**

Potilas saa pasireotidiä 900 mikrog s.c. kaksi kertaa päivässä alkaen leikkauspäivän aamuna, jatkuen 6. postoperatiivisen päivän ilta-annokseen saakka (yhteensä 14 annosta)

##### **2) Perioperatiivinen kortisonihoito**

Potilas saa hydrokortisonia 100 mg i.v. kolme kertaa päivässä alkaen leikkauspäivän aamuna, jatkuen 2. postoperatiivisen päivän ilta-annokseen saakka (yhteensä 9 annosta)

Lukuunottamatta ryhmämukaista lääkehoitoa (pasireotidi tai kortisoni) potilaiden hoito noudattaa rutiininomaista normaalia haimaleikkauspotilaiden hoitoa.

## **Tutkimuspotilaat**

### ***Inklusiokriteerit***

- Haimaleikkaukseen tuleva potilas (pankreatikoduodenektomia, distaalinen resektio, enukleatio, tai muu resektio)

### ***Eksklusiokriteerit***

- Tietokonetomografiassa atrofinen haima tai merkittävästi laajentunut haimatiehyt, haiman osassa johon haimasuolisauma tullaan rakentamaan (koskee vain pankreatikoduodenektomiaan tulevia potilaita).
- Potilaalle suunnitellaan totaalipankreatektomia
- Allergia tai muu kontraindikaatio kortisonille tai pasireotidille
- Ikä < 18 v
- Ei annettua kirjallista suostumusta

### **Kriteerit poistaa potilas tutkimuksesta randomisaation jälkeen:**

- Haimaresektiota ei tehdäkään (esim. levinnyt syöpä)
- Haima on kova ja/tai haimatiehyt on laaja (ns. pienen riskin haima) (koskee vain potilaita, joille on tehty pankreatikoduodenektomia - päätös tehdään intraoperatiivisesti)
- Potilaalle tehdäänkin totaalipankreatektomia
- Potilas haluaa keskeyttää tutkimuksen (keskeyttämiseen mennessä kerättyjä tietoja käytetään tutkimuksessa).

HUOM! Sökkouttamisen purkaminen ja tutkimuslääkkeen ennenaikainen lopettaminen ei poista potilasta tutkimuksesta.

## **Satunnaistaminen**

Potilaat satunnaistetaan 1:1 saamaan joko perioperatiivinen pasireotidi tai kortisoni hoito. Satunnaistaminen tehdään tietokoneavusteisesti käyttäen vaihtelevaa blokkikokoa. Kaikki potilaat, jotka täyttävät inklusiokriteerit, eikä eksklusiokriteerit täyty satunnaistetaan, ja arvotun ryhmän mukainen hoito aloitetaan ennen leikkausta. Randomisaatioryhmän kertova lappu laitetaan kirjekuoreen, josta ei näy läpi (ns. turvakuori). Kirjekuoret numeroidaan, ja ne avataan numerojärjestyksessä.

## **Sökkoutus**

Koska toinen lääke annetaan s.c. ja toinen i.v., ei potilaita tai hoitohenkilökuntaa voida sökkouttaa. Tutkimus tehdään ns. yksöissökkeutetusti, jolloin hoitavat lääkärit ja tutkijat eivät tiedä kumpaan ryhmään potilas kuuluu. Potilaan ryhmän kertovan kirjekuoren avaa potilasta hoitava hoitaja, joka kirjaa Mirandan lääkelistalle lääkkeen nimeltä "haimafistelitutkimuslääke", ja sen lisätietoihin tarkemmin kumpi lääke on kyseessä. Näin ollen lääkärit eivät tiedä kumpaa lääkettä potilas tulee saamaan. Lääkkeiden annot ajoitetaan niin, että ne tapahtuvat vasta lääkärin kierron jälkeen, jotta annettava lääke ei paljastu lääkäreille. Mikäli hoitavilla lääkäreillä on tarve tietää kumpaa lääkettä potilas on saanut (esim. merkittävä haittavaikutusepäily, hoidon muutos, tms), puretaan sökkoutus, ja

lääkäri voi käydä katsomassa kumpaa lääkettä potilas on saanut. Sökkoutuksen purkamisesta/purkautumisesta tehdään aina merkintä Mirandan määräysosioon (ns. nuijan alle) tai sairaskertomustekstiin KIR-lehdelle.

## **Tutkittavat muuttujat**

### **Päävastemuuttuja**

Comprehensive complication index 30 vrk postoperatiivisesti

### **Sekundaariset vastemuuttujat**

1. Komplikaatiot (Clavien-Dindo luokitus), 30 vrk
2. Haimafisteli esiintyvyys ja vaikeusaste (ISGPS luokitus), 30vrk
3. Delayed gastric emptying esiintyvyys ja vaikeusaste (ISGPS luokitus), 30vrk
4. Post-pancreatectomy hemorrhage esiintyvyys ja vaikeusaste (ISGPS luokitus), 30vrk
5. Sairaalassaoloaika, päiviä
6. Readmissiot, 30vrk
7. Adjuvanttihoidon aloittaneiden potilaiden lkm/syöpäpotilaiden lkm

### **Tertiäriset vastemuuttujat**

1. Overall survival, 1, 5, 10v
2. Disease-free survival, 1,5, 10v
3. Disease-specific survival, 1, 5, 10v

Vastemuuttujat analysoidaan myös alaryhmittäin: 1) Potilaat, joille tehty pankreatikoduodenektomia, 2) Potilaat, joille tehty distaalinen haimaresektio.

## **Seuranta**

Potilaita seurataan normaalin rutiiniprotokollan mukaisesti, joko HYKS:ssä tai lähettävässä sairaalassa. Mikäli seuranta tapahtuu muussa sairaalassa, pyydetään näistä sairaaloista sairaskertomustekstit 1, 5, ja 10v leikkauksesta. Tutkimukseen ei kuulu ylimääräisiä kontrollikäyntejä.

## **Kustannukset**

Tutkimukseen otettaville potilaille on tällä hetkellä HYKS:ssä rutiinihoitona perioperatiivinen pasireotidihoito. Tutkimuksessa randomoidaan potilaan 1:1 joko pasireotidihoitoon tai kortisonihoitoon. Kortisoni on halvempaa kuin pasireotidi, joten tutkimus ei aiheuta lisäkustannuksia, vaan päinvastoin vähentää kustannuksia. Hydrokortisoni (Solucortef) 100mg injektio maksaa 5,97 euroa, joten tämän haaran lääkekustannukset ovat yhteensä 53,73 euroa. Pasireotidi (Signifor) 900mikrog injektio maksaa 73,68 euroa, joten tämän haaran lääkekustannukset ovat yhteensä 1031,52 euroa.

